## Ethics and dissemination

### Ethical approval

Ethical approval has been obtained from Berry College’s Institutional Review Board located in northwest Georgia [protocol number 2018-19-24]. At the first baseline testing session, informed consent will be obtained via an informed consent document. Participants will be encouraged to direct any questions about the study to [name]. After reading and signing the document, participants will be officially enrolled in the study. Participants will be able to request a copy of the signed consent document following the baseline assessment. Any modifications to the protocol will be monitored via a manual of operating procedures and reported immediately to the Berry College Institutional Review Board, investigators, and trial registries.

### Safety reporting

#### Risks

The risks to participants are considered to be low and no more than typical daily life. There is little serious risk associated with the completion of the incremental exercise test and exercise sessions. The completion of maximal exercise always involves risks of death, acute myocardial infarction (i.e., heart attack), and complications that require hospitalization. There are risks of slips, trips, and falls during the assessment of functional ability. There are potential risks of becoming frustrated when completing the cognitive assessments. This will be reduced by providing clear instructions and practice tests. We will fully inform participants of the risks associated with the cognitive measures in the informed consent document. Participants will be allowed to discontinue their participation in the study at any time.

#### Protections against risk

All efforts will be made to protect against or minimize all potential identified risks. All participants will be informed of the risks associated with study participation in the informed consent document.

Risks associated with aerobic capacity outcomes and exercise training will be minimized by screening for individuals with factors placing them at increased risk for complications. All personnel will be trained in CPR and emergency lab procedures and will call 911 and [name] in the event of a serious adverse event as outlined in Berry College’s policies and procedures. Importantly, exhaustion, fatigue, and muscle soreness are associated with maximal aerobic exercise and strength testing, but are temporary symptoms. Participants will be encouraged to warm-up and/or stretch before any assessment of fitness or exercise session in order to minimize these symptoms. Participants will further wear clothing appropriate for exercise. Environmental regulation (e.g., use of a fan) will keep the participant cool during the sessions and avoid symptom exacerbation. Risks associated with motor function assessments will be minimized by allowing for the use of assistive devices (i.e., ankle-foot orthoses, canes, and walkers) during testing as well as having a gait belt around the participants’ waist and a research assistant within arm’s reach for stabilizing the participant in the event of a slip, trip, or fall. The testing will further be conducted in a hallway or close to a wall such that participants are able to stabilize themselves when necessary. Risks associated with the cognitive outcomes will be reduced by providing clear instructions and practice tests.

#### Reporting of adverse or serious adverse events

Participants will be instructed to notify research staff immediately when an adverse or serious adverse event occurs. [name] will report the AE or SAE to the Berry College Institutional Review Board. This report will include information on the event type, event severity, event expectedness, study relatedness, description of the event, and any and all steps and actions taken in response to the incident or to resolve the issue.

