#### Process log

A process log will be maintained on a password-protected database to assess enrollment patterns and study feasibility. The log will contain the following demographic information: identification number, individuals’ name, and contact information. The log will also be used to track screening date, eligibility status, date enrolled, reason for ineligibility, reason for refused consent/participation, adherence, and source of subject (e.g., referral, advertising, advocacy, etc.). We will record adherence with the intervention via log books to be filled out at each completed or missed exercise session.

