**Management** (i.e., data management and safety reporting assessment)	1. IRB approval procedures 2. Time and accuracy in data collection, entry, and checking	1. All Institutional Review Board (IRB) approval procedures will be documented and will include communications between the University IRB and staff, and time from submission of IRB application to approval. 2. Data will be checked for completeness and errors. All time spent collecting, entering, and checking data will be recorded.	1. Details procedural and staff requirements for obtaining ethical approval, compliance, and monitoring. Highlights optimal safety procedures to be implemented. 2. Identifies staff time requirements and highlights considerations for alterations to ensure proper data management.
**Scientific** (i.e., safety, burden, and treatment effect assessment)	1. Adverse events, serious adverse events, and clinical emergencies 2. Participants’ experience, burden, and perceptions 3. Treatment effect	1. Adverse events, serious adverse events, and clinical emergencies will be reported and recorded. A safety plan will be enacted in the occurrence of an adverse event wherein participants will be asked to discontinue the HIIT exercise and cool-down (if currently exercising) and will be required to be free of symptoms for at least 48 h before returning to activity. 2. Participants’ experience, burden, and perceptions of intervention appropriateness will be assessed via a short survey at the end of the intervention. 3. Treatment effects will be determined via effect size and clinical meaningfulness calculations of any change in the efficacy outcome variables.	1. Establishes the safety and feasibility of the intervention and identifies considerations for alterations. 2. Determines the acceptability and highlight considerations for alterations. Identifying compliance will further allow correct conclusions to be drawn from the results. 3. Establishes data for power calculations and projected clinical impact.

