### Exercise intervention

The intervention will involve 12 weeks of supervised, progressive (i.e., intensity increases after midpoint testing based on reassessment of aerobic fitness) HIIT sessions two to three times per week. Participants are allowed to choose and alter their frequency of exercise sessions per week as long as they train a minimum of two times per week. The average frequency chosen by participants will inform preferential frequency for future iterations of the study. HIIT exercise sessions will be manualized and led by exercise leaders (i.e., Drs. [name] and [name]). Staff researchers will provide additional safety and monitoring support during each exercise session and assist with data collection and entry. All personnel will undergo training prior to exercise session data collection to ensure standardized sessions.

The individual HIIT sessions will involve 10 cycles of 60-s intervals at the wattage associated with 90% VO_2peak_ followed by 60 s of active recovery intervals at 15 W, totaling 20 min in length (see Fig. 3) [24, 25]. All exercise sessions will begin and end with a 5-min warm-up and cool-down, respectively. Required power output for each interval of the exercise session will be individualized and completely automated using the SciFit FitKey software. VO_2peak_ from baseline (T1) will be used to determine exercise intensity for weeks 1–6. VO_2peak_ from midpoint (T2) will be used for determining exercise intensity for weeks 7–12. Participants will be encouraged to maintain a stepping rate of ~ 80 steps per minute throughout the exercise session [41]. Heart rate will be measured and recorded every minute to characterize the demands of the protocol. Average wattage and steps per minute will be recorded at the end of each interval minute. RPE will be measured every minute and session RPE will be measured at the end of each session using the Borg CR-10 RPE scale [48].

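### For events between sessions, the only stated route to staff is the participant's own report, so the adverse event count may be too low

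*Protocol article*

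**What the plan says.** The section Reporting of adverse or serious adverse events opens with the only step that describes how an event comes to staff's attention: "Participants will be instructed to notify research staff immediately when an adverse or serious adverse event occurs". The rest of that section concerns the onward report to the Institutional Review Board.

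Table 1 (Feasibility metrics, Scientific row) lists adverse events first among the scientific outcomes. It says "Adverse events, serious adverse events, and clinical emergencies will be reported and recorded", without saying how they are elicited, and gives the purpose as follows: "Establishes the safety and feasibility of the intervention and identifies considerations for alterations". The same row requires a participant with an event to be "required to be free of symptoms for at least 48 h before returning to activity".

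On contact and records, Exercise intervention provides for supervised "HIIT sessions two to three times per week" and adds: "Staff researchers will provide additional safety and monitoring support during each exercise session and assist with data collection and entry". Process log says: "We will record adherence with the intervention via log books to be filled out at each completed or missed exercise session". Table 1 (Resource row) also uses individual log books for testing and training requirements, and a database for contacts between participants and staff. None of these is said to carry a question about adverse events.

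Protections against risk says that "exhaustion, fatigue, and muscle soreness are associated with maximal aerobic exercise and strength testing, but are temporary symptoms".

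**The concern.** Under the text as written, an event away from the laboratory enters the data only if the participant recognises it as an adverse event and raises it. The events most plausible there are a fall at home, symptoms that worsen hours after a session, a relapse, or whatever lay behind a missed session or a withdrawal. People who stop attending have the fewest occasions to mention anything, and the survey described under Participant feedback comes only after the final testing session.

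Incomplete capture can only lower the count. Two things depend on it. The first is the safety description carried forward to the randomised trial. The Discussion says the intervention will be judged safe by meeting the Go/No Go criteria, but the two criteria in Data analysis (session completion and half-standard-deviation change) contain no adverse event element. The descriptive count therefore carries most of the direct safety evidence. The second is the symptom-free interval in Table 1, which staff can apply only to events they know about.

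**Working it through.** The plan gives no adverse event rate, capture proportion or precision target, so there is no figure of its own to reproduce. Two checks are possible.

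**1. How much of the intervention period is directly observed?**

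Inputs: 10 cycles of 60 s work and 60 s recovery (20 min), plus a 5-min warm-up and a 5-min cool-down, give 30 min per session (Exercise intervention). There are 24 prescribed sessions (Data analysis), or 3 × 12 = 36 at the highest permitted frequency. Twelve weeks are 12 × 7 × 24 = 2,016 h.

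- 24 sessions: 24 × 0.5 = 12 h; 12 / 2,016 = 0.60%
- 36 sessions: 36 × 0.5 = 18 h; 18 / 2,016 = 0.89%

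Training sessions thus cover under 1% of the period. Testing visits add some observed time, but their length is not stated.

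**2. What could incomplete capture do to the between-session count?**

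This is an illustration only. Let p be the share of participants with at least one between-session event, and c the share of those participants whose event is recorded. Both are assumptions, and c does not apply to events that staff see. With n = 15 independent participants, all followed:

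- Expected number recorded = 15 × p × c
- P(none recorded) = (1 − p × c)^15

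| Assumed p | c = 1 | c = 0.75 | c = 0.50 | c = 0.25 |
|---|---|---|---|---|
| 0.10 | 20.6% | 31.1% | 46.3% | 68.4% |
| 0.20 | 3.5% | 8.7% | 20.6% | 46.3% |
| 0.30 | 0.5% | 2.2% | 8.7% | 31.1% |

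The cells give P(none recorded). At p = 0.20 the expected number of participants recorded falls from 3.0 (c = 1) to 2.25, 1.5 and 0.75.

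The same point can be read from a clean result. If 0 of 15 participants have a recorded between-session event, the one-sided 95% upper limit for the recorded risk is 1 − 0.05^(1/15) = 18.1%. The limit for the true between-session risk is that figure divided by c:

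- c = 0.75: 0.181 / 0.75 = 24.1%
- c = 0.50: 0.181 / 0.50 = 36.2%

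**The case against.** The strongest objection is that this is a condensed article. Telling participants to report at once is ordinary practice and compatible with staff also asking. The article says that sessions and outcome measures are manualised, and Ethical approval mentions a manual of operating procedures that is not shown. Questioning at each session may be written there. This stands as a limit on how firmly the point can be put. It does not remove it, because the article has a section on this subject and that section fixes a participant-initiated route.

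Second, a reader might infer that adverse events as a whole rest on spontaneous report. The documents do not support that. Sessions are supervised, with heart rate and perceived exertion taken every minute; a researcher accompanies the timed walk, and an assistant stays within reach during motor testing. Notification is also instructed rather than left to chance.

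Third, there are other channels. Participants attend two to three times a week and are contacted 24 h before each session, and contacts are logged with their purpose. The neurological exam, walking, fatigue and depression are measured at T1, T2 and T3. These make some capture likely, and it would be wrong to say that the log books serve adherence alone. But no channel is said to ask about events, and a score at T2 or T3 does not identify a fall or a relapse that has resolved.

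Fourth, a reader might infer that Protections against risk, by calling exertional symptoms temporary, contradicts Table 1 or discourages reporting. Neither is shown. The report to the Board must state whether an event was expected, so an expected event can still be reported. What remains is that the article does not say whether such symptoms are counted.

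Finally, there is no control arm and no adverse event threshold, so a low count would bias no comparison and trip no numerical rule. That is correct. The effect is confined to the descriptive count and the conclusion drawn from it.

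**Conclusion.** The point holds for events between sessions. For these, participant-initiated notification is the only route that the article states, and training sessions occupy only 0.60% to 0.89% of the 12 weeks. The adverse event count may therefore be too low. Events during sessions and testing are observed by staff and are not affected.

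The size cannot be derived from the article. The rise from 3.5% to 20.6% in the chance of recording no participant with an event rests on an assumed 20% event risk and an assumed halving of capture; it shows how sensitive a count in 15 people is, not what will happen. The stronger conclusion that safety will look better than it is does not follow: the text supports a possible bias in a known direction and no more. Since the count is meant to establish safety and the remedy is cheap, the change is worth making.

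**What to change.** - At the start of each session, and at T2 and T3, have staff already present ask a short fixed set of neutrally worded questions about events since last contact: any fall, injury, new or worsened MS symptom, relapse or medical visit. Enter the answers, including negative ones, in the existing log book.
- After a missed session or a withdrawal, use the existing contact to ask the same questions and record whether an event was the reason.
- Report solicited and volunteered events separately, and events observed by staff apart from those between sessions.
- State whether expected exertional symptoms are counted as adverse events, and word Table 1 and Protections against risk to agree. This is a request for a counting definition, not for a particular clinical rule.
- If the operating manual already provides for such questioning, one sentence in the reporting section saying so is enough.

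The cost is a few lines in the log book and about a minute per session, with no new visits or equipment. The downside is that more minor events will be recorded; separate reporting keeps them from obscuring the rest. Participants already enrolled (six by June 12, 2020) may have time under the existing procedure only, and the report should say from what date the questions were asked.

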## Discussion

The proposed study evaluates the feasibility and preliminary efficacy of a 12-week, HIIT program using RSTEP in pwMS-wd (i.e., a PDDS score of 3.0-6.0). This work is driven by preliminary data indicating that an acute bout of HIIT taxes the cardiorespiratory system significantly more than continuous exercise, yet without sustained deleterious effects on walking, gait, cognition, core temperature, mood, or enjoyment in pwMS-wd [24, 25]. Those pilot data are from an acute or single bout of HIIT and suggest that the stimulus is acceptable, safe, and tolerable for inclusion in a chronic exercise-training program.

The proposed study will be the first to evaluate the feasibility of a 12-week HIIT program using adaptive equipment for pwMS-wd. A “feasibility study” informs the pragmatics of a RCT by defining whether an intervention can be done, should we continue with the proposed line of inquiry, and if so, how do we proceed to the RCT [53]. Process, resource, management, and science feasibility outcomes are critical to determining if an intervention is viable or not [28, 32]. Moreover, ideal participant recruitment, participant adherence, staff training, protocol execution, and data management strategies can be established. This is crucial for future research on HIIT exercise in MS. The use of a priori Go/No Go Criteria for advancement to a RCT further contributes to the strength and clarity of the proposed design. Such an initial examination of HIIT for inducing physical and functional improvements in pwMS-wd aims to reduce burdens of disability and use objective markers of progress and real-world outcomes.

This proposed study is primarily focusing on the various elements of feasibility with a secondary emphasis on the efficacy results in order to provide strength and clarity to its design [28]. The application of a HIIT paradigm among pwMS-wd is particularly relevant in clinical practice because this population is the most deconditioned of those with MS and experiences limited success with typical pharmacological methods [8, 9, 54]. Some evidence suggests that HIIT is better than continuous, moderate exercise for improving aerobic capacity, increasing ventilatory threshold, and enhancing gait economy in samples of healthy people and those with heart disease [55, 56]. The proposed HIIT protocol, which requires 20 min of exercise in a 1:1 work to rest ratio, has provided the same benefits (e.g., rapid skeletal muscle remodeling towards a more oxidative phenotype) as the traditional HIIT model in healthy adults [56]. Thus, the proposed HIIT paradigm is moving towards a much stronger stimulus for those with MS who have mobility disability.

The use of RSTEP is another innovative aspect of the study that is critical to achieving the intensity prescribed in the proposed paradigm as it removes many of the balance- and function-related issues inherent to treadmill and cycle ergometry exercise in pwMS-wd [8, 57] while utilizing the same motor activation patterns as walking [21, 22]. RSTEP has been recommended as an appropriate and viable assessment tool for evaluating cardiorespiratory fitness in neurological disorders [58], and a recent study has confirmed its efficacy for fitness assessment in MS [8]. Because graded exercise tests using RSTEP generate peak aerobic capacity values typically higher than other modalities [8], the use of RSTEP in the proposed exercise intervention will likely yield exercise prescriptions set at substantially higher workloads [8]. RSTEP further uses both the arms and the legs to generate power. Arm function is critical to the quality of life in pwMS-wd [59], yet rehabilitation specialists typically focus on ambulation. The proposed modality may have the added benefit of improving upper arm function, which would not necessarily occur in interventions using treadmills and cycle ergometers as they do not engage the arms to the same degree.

The proposed study is not without limitations. The first relates to the absence of a control group. No control group will be used because we specifically aim to identify the feasibility and preliminary efficacy of the HIIT exercise protocol alone in pwMS-wd. Once the intervention has been deemed safe and scientifically efficacious through meeting the Go/No Go Criteria set forth in the proposed study design, future iterations of the study will include a control group engaging in MICE. Another limitation to the current study is that it is lab-based and requires that participants provide their own transportation. All efforts will be made to coordinate transportation with participants, including the use of para-transit services within the immediate area. Transportation will be included as a possible reason for declining participation in the study during recruitment. Finally, the inclusion/exclusion criteria limit the generalizability of the study to those who have MS, report walking dysfunction but are able to walk 25 ft, and are under the age of 65. Although the proposed range of participants (i.e., PDDS scores of 3–6) is wide, all participants within this range report at minimum gait impairment and at maximum are primarily wheelchair users but are able to walk 25 ft in under 2 min. Using this wide range will allow us to answer our key question, while maximizing our recruitment potential in a rural, likely underserved population.

As a new rehabilitative approach, HIIT has led to significant benefits in persons with MS who have mild disability, other clinical populations, and healthy populations [18, 19, 56, 60, 61]. HIIT presents a paradigm challenge for pwMS-wd, however, as this population seemingly should not engage in high-intensity exercise—our published pilot data challenge that paradigm as will the proposed research. The proposed research may create a shift among exercise rehabilitation programs for pwMS-wd that is synonymous with the exercise revolution that occurred in cardiac care [62] by demonstrating that a HIIT intervention is feasible and provides a significant stimulus to successfully condition severely deconditioned pwMS-wd. Future studies may generate data on the effects of HIIT in pwMS-wd on motor learning capacity and possible alterations to brain structure and integrity.

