## Methods

### Recruitment

The study will recruit 15 pwMS-wd (i.e., a PDDS score of 3–6) from areas surrounding Berry College. Berry College is located in a highly accessible, rural area in the northwest of Georgia. We will recruit from areas between Atlanta, GA; Chattanooga, TN; and Birmingham, AL. Participants will be asked to provide their own transportation to Berry College. With regard to the sample population, this study focuses on the effects of HIIT in those with MS who are ambulatory, but report walking impairments, as this represents upwards of 75% of the MS community. Although the proposed range of participants (i.e., PDDS scores of 3–6) is wide, all participants within this range report at minimum gait impairment and at maximum are primarily wheelchair users but are able to walk 25 ft in under 2 min. Using this wide range will allow us to answer our key question, while maximizing our recruitment potential in a rural, likely underserved population. We will examine medication use, symptoms of spasticity, and depression in the study results.

Recruitment will occur through fliers provided to local and regional MS Society chapters, clinics, and doctor’s offices; flyers provided at local and regional MS Society events; advertisements on social media; email communication to the local and regional MS Society participants; and by word of mouth. This study will be described as an opportunity to participate in a study testing physiological and functional responses to exercise in persons with MS. Participants will be asked to contact the laboratory by telephone or email for further information about the study and screening for inclusion. See Fig. 1 for a diagram of participant movement from recruitment through completion of the program and Fig. 2 for the schedule of enrollment, intervention, and assessments.

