### Data analysis

All data will be entered, checked, and analyzed using SPSS Statistics (Chicago, IL). All data will initially be de-identified and checked for normality, outliers, errors, and missing entries. Process, resources, management, and scientific feasibility will be examined via descriptive statistics, percentage, and frequency analyses. The effect of the intervention will be determined using a repeated measures, 1-factor analysis of variance (Time) to identify significant changes over time. Multiple comparisons will be corrected using the Bonferroni correction. Disease type, medication use, symptoms of spasticity, and depression will be described and considered in the reporting of the study results. Overall effect sizes will be expressed as partial eta-squared, and small, medium, and large effects will be interpreted as values of 0.01, 0.06, and 0.14, respectively [49]. Feedback data will be reported via descriptive statistics, percentage, and frequency analysis.

We are defining clear Go/No Go Criteria for advancement to a RCT comparing RSTEP HIIT with MICE such that (1) 80% of participants (i.e., 12 participants) must complete at least 20 of the 24 prescribed sessions (i.e., 83%); this criterion is based on an expected dropout rate of ~ 15% [50]; (2) a clinically meaningful change in aerobic capacity and at least one additional outcome measure is required. Among those who successfully complete the trial (i.e., 83% of prescribed sessions), a half standard deviation improvement is necessary in aerobic fitness and at least one of the following outcomes: physical activity, walking, upper arm function, cognition, fatigue, or depression scores; this criterion is based on the universality of a half standard deviation threshold for detecting changes in health-related outcomes in chronic diseases [51, 52].

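### The Discussion says that meeting the Go/No Go criteria shows the intervention to be safe, but neither criterion contains a safety element, so both can be met despite serious related events

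*Protocol article*

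**What the plan says.** The Data analysis section of the protocol article gives two Go/No Go criteria for advancing to a randomised trial.

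1. **Attendance.** 80% of participants, stated as 12, must complete at least 20 of the 24 prescribed sessions.
2. **Change.** "a clinically meaningful change in aerobic capacity and at least one additional outcome measure is required". The population and threshold follow: "Among those who successfully complete the trial (i.e., 83% of prescribed sessions), a half standard deviation improvement is necessary in aerobic fitness", together with the same improvement in at least one of physical activity, walking, arm function, cognition, fatigue or depression.

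The limitations paragraph of the Discussion then describes what meeting them will mean: "Once the intervention has been deemed safe and scientifically efficacious through meeting the Go/No Go Criteria", later versions of the study will add a control group.

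Safety data are collected. Table 1 (Feasibility metrics, Scientific row) lists adverse events, serious adverse events and clinical emergencies, and gives as their importance to later studies: "Establishes the safety and feasibility of the intervention and identifies considerations for alterations". The section on reporting of adverse or serious adverse events sends each event to the IRB with its severity, expectedness and relatedness to the study. The Data analysis section treats all feasibility outcomes descriptively. No section gives a harm threshold or ties these data to the Go/No Go decision.

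**The concern.** The article states both the rule and the conclusion to be drawn from it, and the conclusion does not follow. Attendance and improvement among attenders are not measures of harm. This is not a detail left to a fuller document, because the criteria are given numerically and the Discussion cites them as a strength of the design.

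The point matters because the authors' earlier data in this population come from single exercise sessions, so the safety of 12 weeks of repeated sessions has not yet been observed. The article also acknowledges that maximal exercise carries a risk of serious cardiac events. A statement that the programme has been found safe would be carried into the case for the randomised trial on the strength of criteria that never looked at harm.

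**Working it through.** **Inputs.** Planned sample 15, single group (Recruitment). Criterion 1: 12 participants, 20 of 24 sessions. Criterion 2: assessed in those completers only. Expected dropout about 15% (all Data analysis). The article gives no harm rate, so the rates below are assumptions.

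**The plan's own figures.** 0.80 × 15 = 12, and 20/24 = 83.3%. Both reproduce.

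**How much harm the rule leaves unseen.**

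- *Non-completers.* 15 − 12 = 3 participants (3/15 = 20%) may fall short for any reason, serious harm included. Criterion 2 then leaves them out.
- *Completers.* 24 − 20 = 4 sessions may be missed outright. The retention plan allows make-up sessions within the week, and Table 1 allows return to exercise after a symptom-free interval. A participant can therefore have an adverse event, even a serious one, and still count as a success on both criteria.

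**Illustration for criterion 1.** Let X be the number of participants, out of 15, with a harm that ends training before 20 sessions. Take X as binomial with risk h, and assume no other dropout. Criterion 1 is met when X ≤ 3. The chance that it is met although at least one such harm occurred is P(X ≤ 3) − P(X = 0), where P(X = 0) = 1 − P(X ≥ 1).

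| Assumed h | P(X ≥ 1) | P(criterion 1 met) | P(met and X ≥ 1) |
|---|---|---|---|
| 5% | 0.537 | 0.995 | 0.995 − 0.463 = 0.532 |
| 10% | 0.794 | 0.944 | 0.944 − 0.206 = 0.738 |
| 20% | 0.965 | 0.648 | 0.648 − 0.035 = 0.613 |
| 30% | 0.995 | 0.297 | 0.297 − 0.005 = 0.292 |

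**The reason for stopping is not used.** At the plan's expected dropout of 15%, each participant completes with probability 0.85 and criterion 1 is met with probability 0.82. That figure is the same whether all of the dropout is due to harm or none of it is.

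**What 15 participants can show about safety.** With 3 of 15 harmed, the exact (Clopper-Pearson) 95% interval is 4% to 48%. With 0 of 15, the two-sided 95% upper bound is 1 − 0.025^(1/15) = 0.218, about 22%. These figures describe the sample size and would hold with or without a safety criterion. They do not measure the mismatch between the two sections, but they limit what any fix can claim.

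**The case against.** A reader might infer that Go can be declared whatever harms occur. The documents do not support that. Harms that keep more than 3 of 15 participants below 20 sessions fail criterion 1; at an assumed 30% risk of a harm that ends training, the criterion is met only about 30% of the time. Attendance is a real brake, though a partial one: it does not separate harm from other reasons for missing sessions, and it ignores harm in completers.

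A reader might also infer that adverse events are shut out of the decision altogether. That too goes beyond the text. The two criteria are worded as necessary conditions, and nothing makes Go automatic once they are met. The Discussion calls the scientific feasibility outcomes, which include adverse events, critical to judging viability. Events also go to the IRB, which stands outside the Go/No Go rule. What can be said is that adverse events have no stated threshold and no stated link to the criteria.

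On efficacy, the same paragraph of the Discussion gives the missing control group as its first limitation and speaks of preliminary efficacy. The weakness is therefore largely disclosed, and only the phrase itself needs adjusting.

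None of this removes the mismatch. The Discussion attributes the safety conclusion to meeting the criteria, not to a wider review of the feasibility data.

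**Conclusion.** The point holds in a limited form. The Discussion credits the Go/No Go criteria with showing safety, and the criteria in the Data analysis section contain no safety element. Both can be met with up to 3 of 15 participants stopped by harm, and with any number of harms among participants who still reach 20 sessions. The limit of 3 and the disregard of harm in completers follow directly from the rule. The probabilities rest on assumed harm rates, independence between participants and no other dropout; dropout from other causes would use up part of the margin of 3.

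This should be corrected, but the correction is small. It concerns what may be concluded from the rule; it does not show that harms would go unrecorded or unreported.

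**What to change.** Reconcile the Data analysis section with the limitations paragraph of the Discussion by one of two routes.

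**(a) Narrow the conclusion.** State in the Discussion that meeting the criteria shows adherence and within-group change only. Describe safety separately: participants with adverse events and with serious adverse events, over all enrolled, with exact 95% confidence intervals. In Table 1, say that the adverse event data describe safety, not that they establish it.

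**(b) Add a safety element to the Go/No Go rule.** Count it over all enrolled participants, from the events and relatedness already reported to the IRB. The investigators should set its content and limit with the IRB. Two things should be stated openly. The limit was set after enrolment began (six participants by June 12, 2020, per Trial status). And relatedness is recorded to the study, so it also covers the exercise tests. If stopping because of harm is to be part of the element, the reason for stopping should be added to the process log, which does not list it now.

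Under either route the plan should not be worded as if no safety signal had been found, since that would write in a result before the data exist.

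**Cost.** A short amendment and a more modest conclusion. Route (a) changes wording and adds a simple interval. Route (b) also needs agreement with the IRB. Because of the 22% bound at zero events, neither route lets 15 participants establish safety.
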